**2. Start date**

1^st^ June 2015

**4. Abstract**

*Design:*

A pragmatic, randomised controlled trial and economic evaluation to investigate the effectiveness and cost-effectiveness of the self-directed E-Couch social anxiety module versus a waiting list control condition, for reducing sub-clinical social anxiety symptoms in the general population.

*Study Population:*

Respondents (aged 16+) to a direct-to-consumer advertisement placed on national websites who have social anxiety symptoms but do not meet the criteria for social anxiety disorder (this latter group will instead be advised to seek help).

*Intervention and Control:*

Intervention is the E-Couch social anxiety module, a self-guided intervention. Control group receive no intervention and are placed on a waiting list to receive the intervention at the end of the trial. Both groups receive email and text message reminders.

*Outcome Measures:*

Change in self-reported social anxiety score using the Social Phobia Inventory (SPIN). Secondary measures: Brief Fear of Negative Evaluation scale (8 item BFNE-S); SOPHS Social Phobia screener; depression (CES-D); mental wellbeing (SWEMWEBS); quality of life (SF36); use of mental health services; safety events; adherence, retention and attrition rates. All measures at 6 weeks, 3, 6 and 12 months.

*Analysis:*

A mixed effects model will be used to analyse the primary outcome (intention to treat analysis).

*Sample Size:*

2104 participants (1051 per group) will provide 90% power to detect a small between group effect size of Cohen's d=0.2 at 5% two-sided significant level, accounting for a high level of potential attrition of up to 50%.

*Economic Evaluation:*

A prospective economic evaluation, conducted from a NHS and social care perspective, to provide estimates of cost utility and cost-effectiveness.

*Embedded Qualitative Study:*

Interview study with 20 participants at the end of the study to explore issues including acceptability, adherence, retention, attrition. Also, during the study, in the case of high loss-to-follow-up we will also undertake interviews with a sample of up to 10 participants in the intervention arm, who did not complete their 6 week follow up, to understand some of the reasons behind this.

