**5. Lay Summary**

Social anxiety symptoms cause major problems for many people. The problems tend to last for years and people often do not seek help. Seeing a therapist for face-to-face cognitive behavioural therapy is recommended by NICE as the most effective approach for social anxiety disorder. We also know that many people have 'sub-clinical' social anxiety symptoms which cause them problems but are not severe enough to be diagnosed as 'social anxiety disorder'. We know many of these people turn to the internet to look for help where various unguided, self-directed internet-based tools are being made widely available - but there is very little evidence to say whether or not these are helpful.

We propose to test out the value of an internet self-help package (E-Couch) for sub-clinical social anxiety symptoms in the general population in a randomised controlled trial. We intend to provide E-Couch (or the ‘control’ website) to about 2000 people. These people will have social anxiety symptoms but not social anxiety disorder. For the people who are likely to have social anxiety disorder we will direct them to seek evidence-based help from the NHS, as recommended by NICE.

Over a period of 12 months we will measure the effect of using E-Couch self-help on social anxiety symptoms, as well as on quality of life, mental wellbeing, depression and general anxiety, and their use of other sources of help.

Harnessing the internet to help with a common problem among the general population has great potential to deliver low cost, widely accessible public mental health interventions. Our project will also give the opportunity to learn more about the value of using the internet to do this, and what the opportunities and challenges are - for researchers as well as for service providers and the public.

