**6. The Public Health Approach**

The Internet is playing an ever more important role in our social and emotional lives. People go online in large numbers to find self-help solutions for a range of physical and mental health problems, and for broader health-related activities such as diet and exercise. Delivering self-help tools using online platforms offers a low cost and highly scalable approach that could potentially be harnessed by public health practitioners and policymakers seeking to tackle population-wide problems. However, the public health community has been slow to capitalize on this opportunity, and in general the pace of innovation has run ahead of both policymakers and evaluators. Thus, for many of these online self-help approaches, we do not have good evidence as to whether they are helpful or not (despite their wide use). Furthermore, there are also many unanswered generic questions about the value of the internet as a tool for delivering public health interventions.

In this study we will undertake a rigorous trial of an online self-help intervention for social anxiety symptoms in the general population. This is not about treating people with social anxiety disorder (for whom good treatments exist, and are available on the NHS, and recommended by NICE), but about testing the benefit of a novel public health approach to reduce the level of sub-clinical symptoms in the general population.

Building on our previous studies, a public health approach is appropriate for the following reasons: (1) sub-clinical social anxiety symptoms are very common and have a population distribution; (2) there are many people who could potentially benefit from interventions but who do not access them, and we will recruit directly from the population rather than through a service; (3) while there is evidence that therapist-guided internet-based social anxiety applications are effective, there is insufficient research to determine if fully self-directed interventions, which are becoming ever more available, are effective. Therefore research on online self-help is required because people are using it without strong evidence, and because of the potential cost-saving over a supported intervention, especially if applied at a population level.

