We recognize that there are challenges associated with investigating the efficacy of an unproven, unguided, internet-based self-help for social anxiety symptoms. It is not our intention to deny people with social anxiety disorder the opportunity to receive a treatment with an established evidence base, to undertake a study that would conflict with national guidelines on the treatment of social anxiety disorder, to confuse participants in such a way that might delay them seeking other help, or to create problems if they receive other help in parallel. The National Institute for Health and Care Excellence (NICE) recently published their guideline on the assessment and treatment of social anxiety disorder [NICE, 2013]. This recommends that all NHS patients diagnosed with social anxiety disorder should be offered a course of individual cognitive behavioural therapy based on either the Clark and Wells or Heimberg model of treatment. The IAPT (Improving Access to Psychological Therapies) programme offers this therapy. If an individual declines individual CBT therapy then the NICE guideline recommends that they be offered supported self-help – e.g. advice from a therapist coupled with a workbook based on CBT principles. From 2015 the IAPT programme will, on a region by region basis, initiate a new therapist-supported internet-based treatment of SAD. Our final proposed methodology is very much informed by the above considerations and in particular by the NICE guideline; by the need for us to inform and direct people who are identified with a disorder to effective treatments; and by the treatments that will be available during the period of our proposed research. In order to avoid any confusion between what we are offering and what is available and recommended by NICE,we will clearly describe our intervention as a self-guided and unsupported self-help tool and not as therapy. For all these reasons this proposal is about offering self-help to people with sub-clinical social anxiety symptoms; people who meet criteria for social anxiety disorder (from their self-reported scale measurement) will be directed to seek other, more appropriate help according to NICE guidelines.

*Our approach*

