
The E-Couch toolkit is available online for anyone who registers to use it (<https://ecouch.anu.edu.au>). For this study a social anxiety specific tool will be packaged using the e-couch social anxiety content to create the intervention. We do not anticipate high levels of contamination in the control arm – we will not call the intervention ‘e-couch’ in this study (it will be given a new, study-specific name), and e-couch (and the social anxiety elements within the toolkit) are not widely known or used by the UK population. We will measure contamination and use of any other online social anxiety tools through participant self-report at the time of final follow-up, using a bespoke questionnaire asking respondents which of a list of online interventions they have or have not also accessed during the study period. This is a pragmatic study and we would expect some participants to also be seeking other self-help, in both arms of the study.

*Control group*

The control group receive no intervention and are placed on a waiting list to receive the intervention at the end of the trial.

*Study population*

Internet users who consent to take part in a study for self-help with sub-clinical social anxiety symptoms. To be eligible they must have some level of social anxiety symptoms, defined as scoring 13 or more on the SPIN instrument (the population mean is generally 11 or 12, so the score of 13+ was chosen to pick up people with mild symptoms. People who score over 20 are more likely to have social anxiety disorder).

This is an amendment to the original protocol that required eligible participants to score 13-19 on the SPIN instrument. However it became clear after 6 months of recruitment that very few individuals score in this range, and most people with any level of social anxiety symptoms score more highly.

*Recruitment*

We will use advertisements placed on websites including NHS Choices, the NHS website, which receives more than 25 million unique visits per month making it one of the most visited websites in the UK and certainly the most popular health website. It is also a widely trusted source of health information and the NHS branding is known to facilitate recruitment to research studies [Todkill & [name], 2013]. As noted above, the current team used advertisements on the NHS Choices website very successfully in a previous trial of an e-therapy intervention, recruiting 3070 individuals in a 2-week period [[name] et al., 2013].

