*Eligibility screening and consent*

Individuals expressing an interest in the online advert by clicking on a web link will be directed to a University website containing full information on the trial and the opportunity to ask questions of the study team by email or telephone.

They will be invited to complete screening questions which will determine whether they are eligible for participation: they will need to confirm the following: a working email address (to respond to a confirmation email and receive reminders), a mobile phone number (to receive text reminders), and that they are aged 16 or over and resident in the UK. We will exclude people who are currently receiving therapist-guided treatment for social anxiety disorder. If they meet these criteria, they will be asked to provide online consent. In line with our public health approach and the pragmatic nature of this study, our inclusion criteria have been kept very broad. Having given informed consent, participants will know that they are free to withdraw at any time without giving a reason and without it affecting their care.

In providing consent, participants will give their agreement to complete two screening measures (the SOPHS and the SPIN) and to be randomized to one of two conditions (E-Couch intervention or waiting list control). The consent will also give their agreement to be contacted by email and text message to send them study reminders. Separate consent will be sought for any qualitative interview as part of the study. Participants will be eligible if they score 13 or more on the SPIN.

We do not want to delay any form of help-seeking and all participants with a score>19 on the SPIN will be given advice to seek therapist-guided help from the NHS (including IAPT) as their scores indicate they may have social anxiety disorder (note that we have excluded people currently receiving treatment).

In order to inform future research and to support some exploratory analyses of our data we will include the new SOPHS social phobia screener (<http://nimhr.anu.edu.au/mental-health-measures/social-phobia-screener-sophs>) at this screening stage, although it will not be used for screening at the time (only in post hoc analyses).

*Initial trial flow and collection of baseline measures*

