The primary statistical analysis will be carried out on the basis of intention-to-treat (ITT). We will endeavour to obtain full follow-up data on every participant to allow full ITT analysis, but we will inevitably experience the problem of missing data due to withdrawal, loss to follow up, or nonresponse to some questionnaire items. The results from the trial will be prepared as comparative summary statistics with 95% confidence intervals. All the tests will be done at a 5% two-sided significance level. The study results will be reported in accordance with the CONSORT (Consolidated Standards of Reporting Trials) 2010 statements. A full statistical analysis plan will be prepared before the recruitment starts.

To understand participant disposition, a flowchart showing numbers of participants screened, randomised and those who are available for the final analysis populations will be constructed. Reasons for withdrawal, exclusions or losses to follow-up will be shown at each stage during the study by intervention group.

A mixed effects model will be used to analyse the primary outcome (SPIN score), utilising data collected at 6 weeks, 3, 6 and 12 months from randomisation. An interaction between time and randomised group will be fitted to allow estimation of treatment effect at each time point. The model will adjust for the SPIN score at baseline gender.

Analysis of secondary outcomes, such as scores to measure social anxiety (FNE scale), depression (CES-D), mental wellbeing (SWEMWBS), and quality of life (SF36) will be similar to the method used for the primary outcome. Safety data will be analysed using Fisher’s exact or Chi-squared tests. Other binary outcomes will be analysed using generalised linear model with log link function.

For both primary and secondary outcomes we will include subgroup analyses of baseline factors which may influence the intervention effect (moderators). Baseline subgroups will be compared by including interaction terms in the model (baseline subgroup by treatment group interaction). Baseline factors to be compared include: age; gender; educational level; baseline level of sub-clinical social anxiety symptoms

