A prospective economic evaluation, conducted from a NHS and social care perspective, will be integrated into the trial to assess cost and cost-effectiveness of the self-guided internet-based intervention for people with pre-clinical social anxiety symptoms. Primary research methods will be followed to estimate the costs of delivering the intervention, including development and maintenance costs for the website, advertisement costs, and the costs of monitoring participants for safety or other reasons. Taking a NHS and social care perspective means that broader health service and social care utilization costs will be included in the primary economic evaluation. Health service and social care utilisation data will be collected through participant self-report questionnaires administered at baseline, and each follow-up time point. Unit costs for service utilisation will be derived from standard national sources such as Unit Costs of Health and Social Care (PSSRU), NHS reference cost etc. ,and estimated in line with best practice. Costs will be standardised to current prices where possible. Given the fact that the intervention will target people who are unlikely to pursue help from NHS or social care due to the sub-clinical mild nature of the symptoms, we don’t expect the intervention to have significant impact on health and social care costs. On the other hand, these symptoms may impact on people’s social life which leads to loss of productivities due to leaves from work, study, or absent from leisure activities. We will collect data to assess this wider social impact.

The effectiveness of the intervention will be measured using Quality-Adjusted Life Years (QALYs) using the under the curve approach. Quality of life will be measured at baseline, 6 weeks, 3 months, 6 months, and 12 months using the SF-36. The data will be converted into SF-6D health utilities using established UK based utility algorithms and combined with time duration data (e.g. 6 weeks, 3 months, and 6 months according to the follow up time points from baseline) calculate quality-adjusted life years (QALYs). We are using the SF-6D (derived from SF36), which is a widely accepted generic preference-based measure because we have problems to integrate an online version of the EQ5D and portal to our trial design

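### The protocol still describes a sub-clinical, non-disorder population, but the amended entry rule has no upper SPIN limit, so the pooled result and its 90% power refer to a different population

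*Protocol*

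**What the plan says.** **Who the trial is about.** The Abstract describes respondents "who have social anxiety symptoms but do not meet the criteria for social anxiety disorder" and adds that people who do meet those criteria will be advised to seek help instead. The Lay Summary states: "These people will have social anxiety symptoms but not social anxiety disorder". Section 6 states: "This is not about treating people with social anxiety disorder". Section 9 treats the self-report scale as the criterion: "people who meet criteria for social anxiety disorder (from their self-reported scale measurement) will be directed to seek other, more appropriate help".

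**Who is enrolled.** Section 10, Eligibility screening and consent: "Participants will be eligible if they score 13 or more on the SPIN". The Study population paragraph explains that the former requirement of 13–19 was dropped after six months of recruitment because "very few individuals score in this range, and most people with any level of social anxiety symptoms score more highly". Participants above 19 are advised to seek NHS therapist-guided help because they may have the disorder, but they are still eligible and randomised. The only related exclusion is current therapist-guided treatment for social anxiety disorder.

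**What is analysed.** Section 10, Statistical methods, plans an intention-to-treat mixed model adjusted for baseline SPIN, with moderators that include "baseline level of sub-clinical social anxiety symptoms". The Sample size paragraph justifies d = 0.2 partly by the sub-clinical nature of the population. The Economic evaluation describes participants as "unlikely to pursue help from NHS or social care due to the sub-clinical mild nature of the symptoms". The Summary and Follow-up measures paragraphs of section 10 also still call the symptoms or the population sub-clinical.

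**The concern.** The conflict is between statements that are all current. The amendment changed who may enter, but not the description of whom the trial concerns. By the protocol's own account of recruitment, most people eligible under the new rule score above the range that the protocol treated as sub-clinical.

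At stake is what the primary result means. A positive pooled result could be reported as benefit for sub-clinical symptoms when most of the information comes from higher scorers. A null result could be read as failure in sub-clinical people when few were studied. The stated 90% power could be taken to cover the named population, which it does not. The severity moderator, as labelled, does not describe the range of scores that will be in the data.

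**Working it through.** **1. Reproduce the stated sample size.** Inputs from section 10, Sample size: d = 0.2, two-sided 5%, power 90%, attrition 50%.

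n per arm = 2(1.960 + 1.282)² / 0.2² ≈ 526 analysed. 526 / 0.5 = 1052 recruited per arm, 2104 in total.

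The figure reproduces exactly, and power at 526 per arm is 0.900. There is no arithmetic error in the total. That power belongs to everyone randomised, that is, SPIN 13 or more.

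**2. Precision within the former 13–19 range.** Let s be the share of participants scoring 13–19. The protocol gives no count, so s is an assumption. The recruitment statement points to a low value. Those enrolled before the amendment all scored 13–19, which raises s somewhat, but they are described as very few. The 49% row is a deliberately generous upper case.

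- Analysed per arm: m = 526 × s
- Power ≈ Φ(0.2 × √(m/2) − 1.960)
- Effect detectable with 90% power: (1.960 + 1.282) × √(2/m)
- 95% CI half-width in SD units: 1.960 × √(2/m)

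| Assumed s | m per arm | Power at d = 0.2 | d detectable at 90% | CI half-width |
|---|---|---|---|---|
| 5% | 26 | 11% | 0.89 | ±0.54 |
| 10% | 53 | 17% | 0.63 | ±0.38 |
| 20% | 105 | 30% | 0.45 | ±0.27 |
| 49% | 258 | 62% | 0.29 | ±0.17 |
| all randomised | 526 | 90% | 0.20 | ±0.12 |

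For the 10% and 20% rows the formula gives 17.5% and 30.5%, and a t-test calculation gives 17.4% and 30.3%. These are simple two-group comparisons within the stratum. Baseline adjustment and repeated measures would change all rows, and a continuous interaction model would have different precision because it borrows across scores.

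**3. Can the pooled result come from higher scorers alone?** With a common SD, pooled d ≈ s × d(low) + (1 − s) × d(high). Taking s = 10%, no effect at 13–19 and d = 0.3 above, pooled d = 0.1 × 0 + 0.9 × 0.3 = 0.27. Power at 526 per arm is then 99%. This is an illustration; the documents report no effect by severity.

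**4. Which cut-off marks likely disorder?** The protocol gives three:
- Section 10, Study population: over 20
- Section 10, Eligibility screening and consent: above 19
- Section 11: 19 or more

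Scores of 19 and 20 are classed differently depending on which is used, so a sub-clinical stratum is not yet uniquely defined.

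**The case against.** The strongest reply is that the text is out of date but the design is not broken. The amendment and its reason are stated openly. A SPIN score above the threshold signals likely disorder, not a diagnosis. Randomisation makes the comparison valid for SPIN 13 or more. The model already adjusts for baseline SPIN and plans a severity-by-treatment interaction. The protocol nowhere claims 90% power for scores of 13–19, and the stratum figures depend on an assumed share. All of this stands, and it limits the point to what the pooled result may be said to show.

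A reader might infer three stronger conclusions that the documents do not support.

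- *The trial cannot answer its question at all.* The planned interaction can inform the effect at low scores, though imprecisely.
- *The advice to seek help alters the control condition alone.* It goes to every participant above 19 in either arm. Service use is collected at each follow-up, and mediation analyses of other help received are planned.
- *The economic evaluation is invalidated.* Its remark about help-seeking is an expectation, and being advised to seek help is compatible with not doing so. Costs are collected at baseline and every follow-up regardless. Only the description of the symptoms as sub-clinical and mild is out of date.

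The reply also has force on section 9: directing people to other help does not by itself exclude them. The plain conflict with the entry rule is in the Abstract, the Lay Summary and section 6. What does not stand is that the mismatch is only cosmetic, because it decides which population the conclusion names.

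**Conclusion.** The contradiction is real and should be resolved before results are interpreted. The pooled estimate and the 90% power refer to everyone with SPIN 13 or more, and they do not by themselves establish an effect in sub-clinical people without the disorder. That most entrants score above the former range rests on the protocol's qualitative statement, since no proportion is given. Under assumed shares of 5% to 20%, power at d = 0.2 in the 13–19 range is about 11% to 30%, and it reaches only about 62% if nearly half of participants fall there. These figures take the protocol's d and attrition as equal across severity.

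**What to change.** 1. Reconcile the population and objective wording with the entry rule in the Abstract, the Lay Summary, sections 6 and 9, and the Summary, Follow-up measures, Statistical methods, Sample size and Economic evaluation paragraphs of section 10. State that the primary result and the 90% power refer to SPIN 13 or more.
2. Redefine the severity moderator as baseline SPIN over its full range, kept continuous. From the planned interaction model, report the treatment effect with 95% CI at sub-clinical and at higher scores, and state its limited precision.
3. Base any sub-clinical conclusion on that interaction estimate, not on the pooled result alone. A separate low-powered stratum need not be the only permitted source.
4. Reconcile the three disorder thresholds before any categorical split. Reconcile the Abstract, Lay Summary and section 9 with the eligibility paragraph on how people above the threshold are handled. Which rule is right is for the investigators; this review takes no position.

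The cost is revised wording and one further read-out from a model already planned, with no new data. The downside is a less favourable statement of what the trial can conclude about sub-clinical symptoms.
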